#### Development of dengue severity Flex panel

As the main objective of the dengue severity panel is clinical deployment, we will develop a focused proteomics panel of 5–10 biomarkers derived from the mechanism-informed biomarker discovery that follows our integrative omics analysis of severe dengue. Discovery will be performed using the Olink^®^ Reveal platform, which profiles 1034 proteins, and the resulting candidates will be carried forward into a targeted Olink^®^ Flex assay containing the 5–10 prioritized biomarkers. The panel will be validated in both the Guatemala and India cohorts, with subsequent validation in additional independent cohorts.

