### Study cohorts

Blood samples from patients are collected as per the WHO revised 2009 case classification [1] as: (1) dengue without warning signs (DwoWS), (2) dengue with warning signs (DWS) and (3) severe dengue (SD). Additionally, non-dengue samples will be collected from DENV-negative healthy controls (HCs). 100 individuals from each category will be collected in Guatemala and will serve as the discovery cohort, while 150 individuals from each category will be collected from India and serve as the validation cohort. The patient inclusion and exclusion criteria are presented in Table 1. Additional cohorts from Guatemala, Brazil and Honduras will be used for further validation of the dengue severity biomarkers. Validation of any additional cohorts requires a local ethical clearance, as well as approval from both the Swedish Ethical Review Authority and the COMBAT General Assembly.

**Table 1 Tab1:** Inclusion and Exclusion Criteria for patient enrolment

Inclusion Criteria: The criteria for enrolling the patients in the respective groups.
**Group 1**: Dengue without warning signs (DwoWS) Patients presenting with the following symptoms and confirmed positive for dengue infection following anti-dengue IgM or NS1 ELISA (Enzyme-linked Immunosorbent Assay) lab tests. Symptoms are fever along with at least two of the following: • Myalgia, arthralgia • Nausea and/or vomiting • Rashes • Leukopenia
**Group 2**: DENV with warning signs (DWS) Patients with the above symptoms and any of the following clinical signs: • Abdominal pain with tenderness • Persistent vomiting • Fluid accumulation • Mucosal bleeding • Restlessness, lethargy • Liver enlargement >2 cm • Laboratory findings: An increase in hematocrit levels and a rapid decrease in platelet count
**Group 3**: Severe dengue (SD) Patients with: • Severe plasma leakage leading to hypovolemic shock (dengue shock syndrome) and fluid accumulation with respiratory distress • Severe bleeding, such as epistaxis, and internal bleeding, evaluated by a clinician • Severe organ involvement with any of the following symptoms: - Liver AST or ALT ≥ 1000 - CNS: impaired consciousness - Heart and other organs failure
**Exclusion criteria**: Individuals with the following characteristics were not enrolled.

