### Statistical analysis

Differential expression analyses will be conducted separately for transcriptomic, proteomic, metabolomic and glycomic datasets with correction for multiple hypothesis testing. Integrated pathway and network analyses will be used to identify dysregulated biological processes associated with disease severity. Validation analyses will be performed using independent cohorts. As there are no high-dimensional studies with such large proteomics (> 1000 proteins) and metabolomics (> 1000 metabolites) in dengue, we have used the RNASeqSampleSize [16] to calculate the sample size for the RNA sequencing based on prior data for other viruses. Prior data indicates that the minimum average read counts among the prognostic genes in the control group is 5, the maximum dispersion is 0.5 and the ratio of the geometric mean of normalization factors is 1. If the total number of genes for testing is 20,000, the top 100 genes are prognostic and the desired minimum fold change is 2, then we will need to study 67 subjects in each group to reject the null hypothesis that the population means of the two groups are equal with probability (power) 0.8 using the Fisher’s exact test. The FDR associated with this test of this null hypothesis is 0.01. Assuming the 30% loss of samples due to the quality, we will keep 100 samples in each group for the discovery cohorts and 150 samples in each group for the validation cohorts. Beyond the RNA-seq–based calculation, the retained cohort sizes (100 per group in the discovery cohort and 150 per group in the validation cohort, after an assumed 30% attrition for sample quality) are adequate for the proteomic, metabolomic, glycomic and machine-learning analyses. The RNASeqSampleSize estimate is conservative, as RNA-seq interrogates by far the largest feature space (~ 20,000 genes) and carries greater technical dispersion than targeted proteomic and metabolomic platforms. The Olink^®^ Reveal assay measures 1,034 proteins with high reproducibility, and the LC-MS/MS metabolomic platform quantifies ~ 1,200 features, an order of magnitude fewer tests than RNA-seq. The N-glycomic analysis similarly involves a considerably smaller number of quantified glycan features. Because these targeted platforms interrogate substantially fewer analytes with lower technical variability, the sample size derived for RNA-seq represents a conservative bound expected to provide comparable or greater statistical resolution for the proteomic, metabolomic and glycomic comparisons. For the machine-learning analyses, robustness is ensured primarily through dimensionality reduction and feature selection prior to model training, together with the prospective discovery-and-validation design and external cross-site validation.

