### Study status

Prospective recruitment and sampling commenced in January 2025 and is ongoing at all participating sites. As of June 2026, 170 participants had been enrolled across the four study groups (DwoWS, DWS, SD and healthy controls) in the Guatemala (discovery) cohort; recruitment of the India (validation) cohort is initiated in July 2026 following the funding body approval. Recruitment is anticipated to be completed by November 2027, or earlier should the target sample size (100 participants per group in the discovery cohort and 150 per group in the validation cohort) be reached sooner. Because dengue transmission is cyclical and epidemic-dependent, recruitment timelines are contingent on local outbreak dynamics; should enrolment at any site fall behind target, pre-specified additional cohorts and biobanked samples will be accessed as a mitigation strategy, subject to approval by the COMBAT General Assembly.

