Several limitations warrant consideration. As an observational study, COMBAT cannot establish causal relationships between identified molecular signatures and clinical outcomes. Differences in timing of sample collection relative to symptom onset may influence observed molecular profiles. In addition, variability in transmission patterns and diagnostic capacity across sites may affect recruitment rates and cohort composition. Although laboratory-based inclusion criteria strengthen internal validity, they may reduce the ability to capture the full clinical spectrum of dengue-like illness during low-transmission periods. Achieving an appropriate balance between methodological rigor and epidemiological representativeness remains a central challenge in cohort-based infectious disease research. Finally, although we aim to develop a unified biomarker panel applicable across both settings, differences in host genetic background, environmental exposures, and other population-specific factors may limit the identification of a fully overlapping biomarker signature. In such cases, we will develop and validate region-specific biomarker panels while also identifying conserved biological pathways that may support broader cross-population applicability.

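### The Flex panel is to be validated in Guatemala, the cohort that selects it, so the Guatemala result is an internal check and should not count as validation

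*Protocol article*

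**What the plan says.** Study cohorts gives each country one role. On Guatemala it says: "100 individuals from each category will be collected in Guatemala and will serve as the discovery cohort". The Indian sample has the other role: "150 individuals from each category will be collected from India and serve as the validation cohort". The section on multi-omics studies and biomarker identification selects the markers from the Guatemala RNA-seq, protein and metabolite data. Statistical analysis states the general rule: "Validation analyses will be performed using independent cohorts".

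The section on the Flex panel departs from this. Candidates come from 1,034 proteins on Reveal, 5 to 10 go forward to Flex, and then: "The panel will be validated in both the Guatemala and India cohorts, with subsequent validation in additional independent cohorts". The additional independent cohorts are listed separately, so Guatemala here means the discovery cohort and not the further Guatemalan cohort mentioned elsewhere. No held-out Guatemalan subset is described.

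The second primary endpoint is a validated host panel that predicts progression to severe dengue. The endpoint does not say which cohort's result makes the panel validated.

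Two other statements bear on the point. For the machine-learning work, "robustness is ensured primarily through dimensionality reduction and feature selection prior to model training". If no common signature emerges across regions, the Discussion says: "In such cases, we will develop and validate region-specific biomarker panels".

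**The concern.** A panel picked as the best 5 to 10 of 1,034 candidates fits the chance features of the patients who picked it. Testing it in those patients measures that fit as well as any true discrimination. Changing the assay from Reveal to Flex renews the measurement error, but the patients, their outcomes and their biology are the same.

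A primary endpoint is at stake. Read literally, the Flex sentence lets a Guatemala AUROC support the claim that the panel is validated. If India then did less well, the plan would not say which of the two results decides.

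**Working it through.** **The plan's own figures.** The article gives no expected AUROC for the panel. Its one calculation is the RNA-seq sample size, and it reproduces. The per-gene alpha is 100 × 0.8 × 0.01 / ((20,000 − 100) × 0.99) = 4.06 × 10⁻⁵. With mean count 5 v 10, dispersion 0.5 and a two-sided exact negative binomial test, power at 67 per group is 0.804. Allowing for 30% loss, 67 / 0.7 = 95.7, so 96, which 100 covers. This confirms the group sizes but says nothing about panel performance. It does give the usable numbers: 100 × 0.7 = 70 per group in Guatemala and 150 × 0.7 = 105 in India.

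**Simulation inputs.** From the article: 1,034 proteins, panels of 5 or 10, and 100 (or 70 usable) patients per category in Guatemala and 150 (or 105) in India. Assumed: independent standard normal proteins, severe dengue compared with one or both milder groups, and t-test ranking in place of the Random Forest and network steps.

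**Method.** Rank proteins by |t|, where t = (mean₁ − mean₀) / √(s₁²/n₁ + s₀²/n₀), and keep the top k. Fit a linear discriminant with weights w = S⁻¹(mean₁ − mean₀). AUROC is the share of severe/comparison pairs ranked correctly. There were 60 replicates per setting, and cross-validation (CV) used 10 folds.

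**No true signal (correct AUROC 0.50).**

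| Severe v comparison | k | Same data | CV, selected once on all | CV, selected in each split | Locked panel, new cohort |
|---|---|---|---|---|---|
| 100 v 100 | 5 | 0.759 | 0.734 | 0.497 | 0.489 |
| 100 v 100 | 10 | 0.827 | 0.786 | 0.493 | 0.498 |
| 70 v 70 | 5 | 0.803 | 0.773 | 0.519 | 0.499 |
| 70 v 70 | 10 | 0.874 | 0.830 | 0.497 | 0.490 |
| 100 v 200 | 5 | 0.731 | 0.710 | 0.493 | 0.492 |
| 100 v 200 | 10 | 0.790 | 0.756 | 0.498 | 0.500 |

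The new cohorts were India-sized: 150 v 150, 105 v 105 and 150 v 300.

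**Twenty truly different proteins (assumed): same-data AUROC minus new-cohort AUROC.**

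| Effect | 100 v 200, k = 5 | 100 v 200, k = 10 | 70 v 70, k = 5 | 70 v 70, k = 10 |
|---|---|---|---|---|
| 0.3 SD | 0.769 − 0.648 = 0.121 | 0.835 − 0.674 = 0.161 | 0.826 − 0.583 = 0.243 | 0.892 − 0.584 = 0.308 |
| 0.5 SD | 0.848 − 0.784 = 0.064 | 0.915 − 0.863 = 0.052 | 0.876 − 0.763 = 0.113 | 0.938 − 0.814 = 0.124 |
| 0.8 SD | 0.935 − 0.894 = 0.041 | 0.979 − 0.960 = 0.019 | 0.953 − 0.897 = 0.056 | 0.984 − 0.956 = 0.028 |

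The excess shrinks as the signal strengthens. The locked panel in a new cohort shows no selection bias.

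**The case against.** The strongest reply is that the design already contains a real external test. India is named as the validation cohort, a secondary endpoint calls it independent, and "Additional cohorts from Guatemala, Brazil and Honduras will be used for further validation of the dengue severity biomarkers". Running Flex in Guatemala is also a sensible analytical step, since the Flex panel's analytical performance is itself part of a secondary endpoint. Both points stand. They limit the finding to the Guatemala result and the name it is given.

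Four stronger readings are tempting, and the article does not support them.

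- *All reported performance is inflated.* It is not. A panel locked on Guatemala and tested in India is free of this bias.
- *Selecting features before training is leakage.* The phrase gives an order of steps and is compatible with selection inside each training split. The same sentence goes on to rely on the discovery-and-validation design and on external testing across sites. Selection on all samples is nowhere stated, and fold-level detail may properly sit in a fuller document.
- *A failed India validation will be turned into an India panel tested on the same patients.* The Discussion does not say so. Study setting lists three Indian hospitals and leave-one-site-out validation is planned, so a held-out test is feasible. What remains is that no additional Indian cohort is named.
- *Validation cohorts will be used up to fill enrolment.* If recruitment lags, "pre-specified additional cohorts and biobanked samples will be accessed as a mitigation strategy", subject to consortium approval. The article does not say that a cohort so used would also count as external validation.

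A complete absence of signal is a worst case, too. The article itself cites earlier work linking protein changes to severity.

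**Conclusion.** The contradiction is real and confined to one sentence. The Flex section calls a re-test in the discovery cohort validation, against the cohort roles in Study cohorts and the independence rule in Statistical analysis. The Guatemala AUROC would be too high by an amount that depends on a signal nobody yet knows: about 0.02 to 0.06 if 20 proteins differ by 0.8 SD, 0.05 to 0.12 at 0.5 SD and 0.12 to 0.31 at 0.3 SD. With no signal at all, the panel would score 0.73 to 0.87 against a true 0.50.

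These sizes rest on the independent normal proteins, t-test ranking, 20 true proteins and choice of contrast assumed above. Correlation between proteins would reduce the optimism somewhat. The conflict between the passages does not depend on any of these assumptions.

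Two points are conditional. If outcome-based selection were done once on all samples, cross-validated results would leak (0.71 to 0.83 with no signal, against 0.49 to 0.52 with selection in each split). If the region-specific fallback were used, an India panel would need Indian patients who did not help derive it.

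**What to change.** - **Flex panel section:** describe the Guatemala Flex run as an internal, technical-transfer check. State that proteins, coefficients and cut-offs are locked before outcome-linked India data are opened.
- **Primary endpoint:** state that only India, and later cohorts untouched by discovery, count as validation of the panel.
- **AI models and Statistical analysis:** add that any internally cross-validated result repeats outcome-based feature selection inside each training split.
- **Region-specific fallback:** call an India-specific panel exploratory unless it is tested on Indian patients not used to derive it, for example those of a held-out hospital.

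The cost is a few sentences and some computing time. Study status puts the start of India recruitment at July 2026, so the lock can be laid down before those outcomes are analysed. The downside is that the performance figures from Guatemala will look less favourable.

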### Statistical analysis

Differential expression analyses will be conducted separately for transcriptomic, proteomic, metabolomic and glycomic datasets with correction for multiple hypothesis testing. Integrated pathway and network analyses will be used to identify dysregulated biological processes associated with disease severity. Validation analyses will be performed using independent cohorts. As there are no high-dimensional studies with such large proteomics (> 1000 proteins) and metabolomics (> 1000 metabolites) in dengue, we have used the RNASeqSampleSize [16] to calculate the sample size for the RNA sequencing based on prior data for other viruses. Prior data indicates that the minimum average read counts among the prognostic genes in the control group is 5, the maximum dispersion is 0.5 and the ratio of the geometric mean of normalization factors is 1. If the total number of genes for testing is 20,000, the top 100 genes are prognostic and the desired minimum fold change is 2, then we will need to study 67 subjects in each group to reject the null hypothesis that the population means of the two groups are equal with probability (power) 0.8 using the Fisher’s exact test. The FDR associated with this test of this null hypothesis is 0.01. Assuming the 30% loss of samples due to the quality, we will keep 100 samples in each group for the discovery cohorts and 150 samples in each group for the validation cohorts. Beyond the RNA-seq–based calculation, the retained cohort sizes (100 per group in the discovery cohort and 150 per group in the validation cohort, after an assumed 30% attrition for sample quality) are adequate for the proteomic, metabolomic, glycomic and machine-learning analyses. The RNASeqSampleSize estimate is conservative, as RNA-seq interrogates by far the largest feature space (~ 20,000 genes) and carries greater technical dispersion than targeted proteomic and metabolomic platforms. The Olink^®^ Reveal assay measures 1,034 proteins with high reproducibility, and the LC-MS/MS metabolomic platform quantifies ~ 1,200 features, an order of magnitude fewer tests than RNA-seq. The N-glycomic analysis similarly involves a considerably smaller number of quantified glycan features. Because these targeted platforms interrogate substantially fewer analytes with lower technical variability, the sample size derived for RNA-seq represents a conservative bound expected to provide comparable or greater statistical resolution for the proteomic, metabolomic and glycomic comparisons. For the machine-learning analyses, robustness is ensured primarily through dimensionality reduction and feature selection prior to model training, together with the prospective discovery-and-validation design and external cross-site validation.

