### Study procedures

A single blood sample is collected from the non-hospitalized patients, while two blood samples per participant are collected from the hospitalized patients. The first one is taken within the first two days of hospitalization, and the second at discharge. A questionnaire is administered at the time of blood collection (Table 2). Total participation time is less than 15 min. For Guatemala, whole blood is collected in Tempus™ tube for transcriptomics and in Cytodelics medium for flow cytometry, while plasma from EDTA blood and serum are collected for proteomics, metabolomics and glycomics. For India, whole blood (3 ml) is collected in Tempus™ tubes for transcriptomics and 7–8 ml in BD Vacutainer CPT™ Cell Preparation Tubes for plasma separation and PBMC isolation.

**Table 2 Tab2:** Routine clinical investigations performed in dengue cases in all the cohorts

Parameters	Unit of Measurement
Age	In years
Sex	Male/Female

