**Clinical biochemistry**	
Hemoglobin	g/dL
White Blood Cells	(value)/µL
Differential Lymphocyte Count (eosinophils, neutrophils, lymphocytes)	(value)/ µL
Platelets	(value)/ µL
Hematocrit	%
Procalcitonin	mcg/L
Total bilirubin	mg/dL
Aspartate Transaminase	IU/L
Alanine Transaminase	IU/L
Alkaline Phosphatase	U/L
Urea	mg/dL
Creatinine	mg/dL
Partial Thromboplastin Time	seconds
Activated Partial Thromboplastin Time	seconds
Serum Lactate Dehydrogenase	U/L
Lactate Oxidase (Arterial Blood Gas)	mg/dL
Creatinine Phosphokinase	U/L
Troponin T	ng/mL
N-Terminal Pro- B-Type Natriuretic Protein	pg/mL

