#### Multi-omics studies and biomarker identification

We will perform RNA sequencing (RNA-seq) of the blood cells [10], proteomics by Olink^®^ Reveal, and metabolomics using liquid chromatography-mass spectrometry (LC-MS/MS) in the samples collected from Guatemala [11, 12]. Due to different numbers of analytes, i.e., genes from RNA-seq (n = ~ 20000), protein (n = ~ 1034) and metabolites (n = ~ 1200), we will first identify biomarkers associated with disease severity in each omics dataset using Random Forest for feature selection, and Bayesian belief network (BBN) based structural causal modelling to infer putative causal relationships [12]. To further refine the biomarkers, we will perform integrative analysis using the Consensus Association (CA) analysis and gene/protein/metabolite cooperation networks by integrating the transcriptomics, proteomics and metabolomics analysis to identify a robust mechanism-informed protein biomarker panel for clinical translation [9]. Additionally, a high-throughput analysis of total plasma, IgG, and/or IgM N-glycome [13, 14] from the available patient cohorts will be performed to evaluate glycosylation as a biomarker of disease severity. For Indian samples we will perform RNA-seq of the blood cells and proteomics by Olink^®^ Reveal.

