#### Personalized GEM to bridge and improve the ex-vivo cell-based DENV-GEM

To further improve a DENV GEM developed in an ex vivo assay, we will add the patient-based GEM both from bulk sequencing and scRNA-seq data to improve the predictability of the immunomodulator. We will use the personalized GEM developed recently to avoid heterogeneity by adding the viral biomass objective function (VBOF). We will provide feedback on the essential gene-metabolite knock-out (KO) module to the initial DENV-GEM to improve the identification of the immunomodulator [10].

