#### Secondary endpoints

Dysregulated immune and metabolic pathways associated with disease severity, identified through integrative multi-omic analysis.Reproducibility of candidate biomarkers and pathways in the independent India (validation) cohort and additional external cohorts.Discrimination and calibration performance of machine-learning models integrating clinical, laboratory, demographic, virological and multi-omics features for severity prediction.Analytical and clinical performance of the focused 5–10 biomarker Olink^®^ Flex dengue severity panel.Associations between DENV serotype, host immunometabolic profile and disease severity.

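### Bulk whole-blood RNA-seq mixes cell composition with per-cell regulation, and the differential expression, pathway, network and metabolic-model analyses as described include no step to separate them

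*Protocol article*

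**What the plan says.** All references are to the protocol article.

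- **Material.** Under Study procedures, for Guatemala, "whole blood is collected in Tempus™ tube for transcriptomics". India uses the same tube type (3 ml). The assay is "RNA sequencing (RNA-seq) of the blood cells" (Multi-omics studies and biomarker identification), and it is used in both countries.
- **Analysis.** Statistical analysis states: "Differential expression analyses will be conducted separately for transcriptomic, proteomic, metabolomic and glycomic datasets with correction for multiple hypothesis testing". It continues: "Integrated pathway and network analyses will be used to identify dysregulated biological processes associated with disease severity". The multi-omics section adds Random Forest selection and Bayesian belief networks meant to suggest causal links. The section on personalized metabolic models says "we will add the patient-based GEM both from bulk sequencing and scRNA-seq data".
- **Endpoint.** A secondary endpoint is "Dysregulated immune and metabolic pathways associated with disease severity, identified through integrative multi-omic analysis".
- **Cell data collected.** Table 2 lists white cells, platelets and "Differential Lymphocyte Count (eosinophils, neutrophils, lymphocytes". Monocytes are not listed. The table is headed "Routine clinical investigations performed in dengue cases in all the cohorts", so healthy controls are not named. Flow-cytometry samples are taken in Guatemala. Single-cell RNA-seq with cell-type annotation is planned in about 20–25% of samples.
- **Stated use of laboratory data.** They enter the machine-learning severity models (Artificial intelligence models for DENV severity). The data management section also says that they will be integrated to support biomarker discovery.

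**The concern.** A gene expressed mainly in one cell type looks down-regulated in bulk data when that cell type becomes scarcer, even if no cell has changed its behaviour. Correction for multiple testing does not help, because this is bias and not chance. Validation in India does not help much either: the tube type and the assay are the same, so a composition effect common to dengue would replicate and look confirmed.

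The group definitions make this more than a theoretical worry. In Table 1, leukopenia is one of the qualifying features of Group 1 and carries over to Group 2, and a rapid platelet fall is a Group 2 laboratory sign. Whole blood contains platelets, and the Discussion cites platelet degranulation among the pathways earlier studies linked to severity. A drop in platelet-derived transcripts could therefore partly restate the case definition.

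At stake is the mechanistic reading: the pathway endpoint, the network inference and the bulk-based part of the metabolic models. Prediction is much less affected, because cell mix can be a legitimate predictor.

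**Working it through.** **1. Reproduce the plan's own figure.** Inputs from Statistical analysis: 20,000 genes, 100 prognostic, control mean count 5, dispersion 0.5, fold change 2, FDR 0.01, power 0.8, normalization ratio 1.

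Per-gene alpha = (100 × 0.8 × 0.01) / (19,900 × 0.99) = 0.8 / 19,701 = 4.06e-5, two-sided critical value 4.104.

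A negative-binomial exact test at this alpha gives power 0.793 at 66 per group and 0.804 at 67. The stated 67 is reproduced. A Wald approximation on the log ratio also gives 67. With 30% loss, 100 per group leaves 70.

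**2. Fold change from composition alone.** For a gene expressed only in one cell type, with per-cell expression unchanged, fold change F = p1 / p0, where p0 and p1 are that cell type's share in the two groups. The documents give no shares, so all values below are assumptions.

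**3. Probability of being flagged.** With F the ratio of means and n per group, the first group's mean being 5:

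v = (1/5 + 0.5) + (1/(5F) + 0.5); probability ≈ Φ( |ln F| / √(v/n) − 4.104 ).

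Worked example, 60% to 30%: F = 0.5 and the mean falls from 5 to 2.5, so v = 0.7 + 0.9 = 1.6. At n = 70, 0.693 / √(1.6/70) = 4.585, and Φ(4.585 − 4.104) = 0.685. At n = 100, 0.693 / √(1.6/100) = 5.480, and Φ(1.376) = 0.92.

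| Assumed shift | F | v | n = 70 | n = 100 |
|---|---|---|---|---|
| Doubling (e.g. 25% to 50%) | 2.00 | 1.30 | 0.84 | 0.98 |
| 60% to 30% | 0.50 | 1.60 | 0.685 | 0.92 |
| 30% to 40% | 1.33 | 1.35 | 0.02 | 0.05 |
| 60% to 50% | 0.83 | 1.44 | 0.002 | 0.005 |

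Direction matters: a fall from mean 5 is harder to detect than a rise, because the lower mean adds sampling variance. These figures are for fully cell-specific genes. A gene that is only enriched in the cell type has a fold change closer to 1 and is flagged less often.

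**4. Look for a correcting step.** Read together, the sections on multi-omics, single-cell sequencing, personalized metabolic models and statistical analysis contain no statement linking the counts, the flow cytometry or the single-cell data to adjustment of the bulk results.

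**The case against.** Several points on the other side have weight.

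- **Absence in a condensed article.** The quoted sentence names no covariates at all, and a covariate list is normally left to an analysis plan that is not shown. That stands: a missing list is not the defect. What remains is the chain that the article itself sets out, from bulk differences to dysregulated pathways, putative causal links and metabolic models.
- **Use of the counts.** A reader might infer that the blood counts are never used. The documents do not support that, since laboratory data enter the machine-learning models and are to support biomarker discovery.
- **Cell-resolved work.** A reader might infer that the study has no means of seeing regulation within cell types. That is wrong. Single-cell sequencing covers 20–25% of samples; if this means participants, it is 80–100 of 400 in Guatemala and 120–150 of 600 in India. It has its own differential expression and pathway analyses, and it contributes to the metabolic models. It is simply not linked to correction of the bulk results.
- **No documented shift in proportions.** Leukopenia is a fall in the total count. If the proportions stay the same, p1/p0 is 1. Leukopenia is also optional within Group 1, and its absence from the Group 3 list does not show that cell mix differs by severity.
- **Over-adjustment.** Cell mix may itself be part of the host response, so keeping only the genes that survive adjustment could discard real signal. This stands, and it is why the fix asks for both results.
- **Limited reach.** The deployable product is a protein panel, and the Discussion already says that the study cannot establish causality. That limitation does not mention cell mix, however.

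**Conclusion.** The point holds for interpretation. As described, the bulk differential expression, pathway, network and bulk-based metabolic-model analyses cannot tell a change in cell mix from a change in regulation, although data that would help are being collected.

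Its size is conditional. At the plan's mean count and dispersion, a halved cell share would lead to its specific genes being flagged with probability about 0.68 to 0.69 at 70 per group and 0.92 at 100; a doubled share gives 0.84 and 0.98. A 10-point shift gives about 0.05 or less. These figures rest on assumed fractions, on fully cell-specific genes and on a Wald approximation.

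A reader might infer that the planned pathway findings will be composition artefacts. The documents do not support that: they report leukopenia and falling platelets but no shift in white-cell proportions. Nor does the point undermine the predictive panel or the stated sample size, which reproduces.

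**What to change.** For the contrasts between dengue severity groups, add a parallel bulk RNA-seq model. Use same-sample white cell count, differential fractions and platelet count as covariates, or use deconvolved cell fractions. Any deconvolution reference must cover neutrophils and monocytes. Table 2 lists no monocytes, and India's cell tubes are for PBMC isolation. The article does not state the single-cell input, so check this before the subset is used as the reference.

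Report adjusted and unadjusted results side by side. Describe a pathway or network signal as altered regulation only if it persists after adjustment; otherwise call it composition-linked. Keep the unadjusted analysis for prediction. For contrasts with healthy controls, use deconvolved fractions, because Table 2 covers dengue cases only.

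The adjustment by measured counts needs no new samples. The costs are extra analysis work (including checking network and metabolic-model signals against the adjusted results), deconvolved fractions where same-sample counts are missing, some loss of significant genes, and possible over-adjustment where cell mix is part of the host response. Reporting both results keeps that last cost visible.
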